### Random assignment and manipulation of treatments

The evaluation will measure outcomes at the child, household and school level. Households and schools will be randomly assigned to the intervention. Three treatment arms are envisaged:

1) Control group. These are schools and households from villages where the intervention will not be implemented. The intervention will be delayed by at least two years in these villages, preferably without informing schools and households.

2) Regular school feeding programme group. These are schools and villages where the standard Government programme is implemented, with mayors responsible for the food procurement.

3) Home grown school feeding and social accountability group (HGSF±). These are schools and villages where the programme is implemented in addition to a capacity building component, including training of community-based organisations and local government on food procurement, nutrition education and feedback monitoring.

Note that in the intervention areas, as per the selection protocol, one school would be linked to one village. Furthermore, two schools in two villages would be selected in each commune. The HGSF+ intervention is conducted at the commune level. Training and monitoring systems involve mayors and exert their effects at the commune level, affecting outcomes in schools where the HGSF+ programme is not implemented. On the other hand, the number of communes where the programme is implemented is rather small, which reduces the statistical power of the analysis, and the effect of the school feeding intervention against the control group are best observed at the school level. Hence, we opted for a design that compares outcomes of school feeding versus a control group at the school level, and that compares outcomes of HGSF+ versus regular school feeding at the commune level. The MOE selected 58 out of the 170 most vulnerable communes in the country where the programme will be implemented. In each of these communes, mayors then selected two schools with similar characteristics that are eligible for the programme. Each school was then randomly assigned either to the treatment or to the school feeding intervention. A protocol was designed in order to ensure that contamination between the two schools in each commune was avoided. This will allow comparison of outcomes of the school feeding intervention against the control group at the school level in 58 communes. A second level randomisation involved randomly assigning the intervention schools in the 58 communes to either the regular school feeding or HGSF+ (or school feeding *plus* the enhanced training package) treatment groups. In practice, the randomisation of the HGSF+ intervention occurred using restricted randomisation at the commune level [25]. To ensure balance in the comparison groups, the random allocation of communes to school feeding or HGSF+ was undertaken by modelling pilot selection using a set of community and district level variables, testing 1,000 random allocations and selecting the permutation that minimises the R^2^ for the predicted selection [26].

Power calculations (see Appendix 1 for more details) and resource availability suggested the adoption of a sample of 25 households from the village areas of the 58 schools receiving the intervention and of 20 households in the village areas of the 58 control schools. Farmers will be oversampled in both areas in the following way: 10 out of the 25 households in the 58 intervention villages will be farmer households and 5 out of the 20 households in the 58 control villages will be farmer households. This distribution of the sample between farmers and non-farmer households and between project control groups allows the construction of comparable samples (see Table 3).

**Table 3 T3:** Summary of sample sizes

	**Communes**	**Schools**	**Households**	**Farmers**	**Children**^**1**^
Control	58	58	870	290	2,700
HGSF	29	29	435	290	1,500
HGSF+	29	29	435	290	1,500
TOTAL	58	116	1,740	870	5,700

Note: 1) the number of children in an estimate based on an average of 2 children per family in families with children and 1.5 children per family in farmer households.

Households were randomly selected in the catchment areas of the selected schools for the survey interviews.^6^ The definition of ‘household’ in Mali is not straightforward as many families share the same living compound and polygamous families are common. A recent study [27] found that adding descriptions to a “restricted” definition of household (a group of people who normally live in your household – adopted by the DHS) increases the number of adult male members reported during the interview. This, however, does have a very limited impact on household characteristics, such as per capita food consumption, assets and agricultural production. We recommend the use of the restricted definition adopted by the Rapid Household Survey 2006, which reflects the LSMS experience in collecting data in developing countries. According to this definition, a (restricted) household is a group of people who normally live and eat together. Members spending less than three months with the household within a year should be excluded. Families living in the same compound should be considered as different (restricted) households, though the consumption section of the questionnaire was carefully designed in order to take into account the common use of food resources. Polygamous households were treated as distinct households if wives live and cook in separate houses.

In practice, the sampling of households was not conducted via a previous census as this was considered too costly in terms of time and resources. We opted for interviewing village chiefs and building a list of enlarged households in the villages covered by the sample school. The listing also included an approximation of the size of the enlarged households. In addition, a number of farmer households was oversampled in each village. Chiefs (and members of the CGSs) were asked to list which farmers they would contact if they were to purchase food within the village for the provision of school meals. This latter information was used to single out the surplus farmers in the area (up to 10 in the project villages and up to 5 in the control villages that will be interviewed).

Enlarged households were randomly selected (with inclusion probability proportional to size) from the list provided by the village chiefs, and listings of the restricted households within each selected enlarged households will then be developed through interviews with household heads. A restricted household with children aged 5 to 15 was then randomly selected within each selected enlarged non-farmer household, and we estimate that each household will have at least two children in this age group. A similar selection procedure was used for farmer households when these exceed the numbers of 10 and 5 in the project and control villages, respectively. In farmer households though, no age criteria were used and the household was identified around the main agricultural holding unit of the enlarged household. This consists of the family members involved in the main production unit (land and livestock) in the enlarged household.

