### The HGSF pilot

An innovative capacity-building component will be integrated alongside the national school feeding programme and will constitute one of the treatment arms of the experiment (see Figure 2). The HGSF pilot intends to promote purchases from small farmers through training, monitoring and communication activities among the actors involved. Mayors and CAPs will be instructed, and encouraged, to involve small farmers in the transactions. Currently, mayors purchase food from one or more traders following government guidelines regarding contracts and bidding processes. Under the project, and in coordination with the Ministry of Agriculture, mayors and traders will be requested to enforce the purchase of food from local producers at least at a minimum percentage. On the other hand, the CGSs will be assigned the task of identifying local suppliers, possibly at the village level, and of establishing contacts between these suppliers and the traders.

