## Discussion

National Governments in sub-Saharan Africa have demonstrated strong leadership in the response to the recent food and financial crises by scaling-up school feeding programmes. “Home-grown” school feeding programmes have the potential to link the increased demand for school feeding goods and services to community-based stakeholders, including small-holder farmers and women’s groups. However, there is a dearth of evidence on the costs and benefits of school feeding programmes linked to small-holder agriculture and community development. This evaluation will be the first to examine the impact of linking school food service provision on small-holder farmer income, as well as the link between community level engagement and programme performance, alongside assessing the more traditional benefits to school children.

The impact evaluation follows a theory-based approach and is underpinned by the development of the programme theory for the intervention. It includes a process evaluation component that will enable policymakers to not only understand if the intervention works or not, but also why and how it is working. By using a mixed-method approach, the evaluation will explore both hard outcomes (for example, enrolment, income, welfare) but also perceptions on softer elements of programme performance (for example, community ownership and accountability).

This study will also be the first evaluation designed around the scale-up of a national school feeding programme in sub-Saharan Africa. It is a prime opportunity to provide policy relevant evidence. To ensure that this was the case, policy makers across Education, Health, Agriculture and Local Government Ministries were engaged from the early design stages through to survey design and implementation. In particular, this study is anchored in the framework provided by the Ministry of Education’s recently developed national school feeding policy. In Mali, the national policy on decentralisation also meant that policy makers at regional and commune level be engaged in design process. A number of meetings were held to sensitise stakeholders at the different levels, also including them in the randomisation process.

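### Farmers were nominated by chiefs and school committees after school allocation, with no masking of the nominators described, so the farm-income samples may differ between project and control villages

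*Protocol article*

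**What the plan says.** All places are in the protocol article.

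- **School allocation** (Random assignment and manipulation of treatments) is reported as completed: "Each school was then randomly assigned either to the treatment or to the school feeding intervention". From the surrounding text this means control versus school feeding.
- **Farmer identification** (same section): "Chiefs (and members of the CGSs) were asked to list which farmers they would contact if they were to purchase food within the village". The number taken depended on arm: "up to 10 in the project villages and up to 5 in the control villages that will be interviewed". Chance entered only for long lists: "A similar selection procedure was used for farmer households when these exceed the numbers of 10 and 5 in the project and control villages, respectively".
- **Role of the nominators.** Under HGSF+, "the CGSs will be assigned the task of identifying local suppliers" (The HGSF pilot). The description of the national programme also allows either the commune or the CGS to buy the food.
- **Knowledge of allocation.** The Discussion says: "A number of meetings were held to sensitise stakeholders at the different levels, also including them in the randomisation process". Concealment is described only for the later roll-out in control villages: "The intervention will be delayed by at least two years in these villages, preferably without informing schools and households". Threats to validity repeats this for teachers and households. Neither place mentions masking chiefs or CGS members.
- **Timing of the HGSF+ allocation.** The design section says "In practice, the randomisation of the HGSF+ intervention occurred using restricted randomisation at the commune level", based on community and district variables. The Conclusions of Appendix 1 put it in the future and base it on baseline village and school data.

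**The concern.** Randomising schools protects the farm-income comparison only if farmers enter the sample in the same way in both arms. Here entry depends on the judgement of local people, asked after their school had been allocated. In a control village the question is purely hypothetical. In a project village, an informant who knows a canteen is coming may have a real purchase in mind and may name farmers who are preparing to produce more.

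A random draw from the list cannot correct who was put on it, and equal caps would not either. Farmer income is a primary outcome, and the article expects only a small number of farmers per village to benefit, so who is listed matters. Threats to validity considers spill-over, Hawthorne-type effects and attrition, but not this route.

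**Working it through.** **1. The plan's own counts.** Villages times cap gives 58 × 5 = 290 control farmers, 29 × 10 = 290 in each feeding arm, and 870 in total. This reproduces Table 3. The sample was therefore drawn with project or control status fixed.

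**2. What the estimator removes.** Let a nominated farmer's mean income without the programme be a at baseline and a + g at follow-up, with subscripts P (project) and C (control), and let τ be the programme effect.

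- Project change: g_P + τ. Control change: g_C.
- Difference-in-difference: τ + (g_P − g_C).

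The levels a_P and a_C cancel, so a fixed baseline gap does no harm. The growth term cancels only if nomination did not depend on arm. Covariate adjustment helps only as far as measured baseline variables predict growth.

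**3. How sensitive the income test is.** Appendix 1 gives ρ = 0.25, B = 0.40, n = 10 farmers per village and K = 58 communes, and treats percentage and standardised differences as almost equal. The between-commune variance of the effect, s², is not given.

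- Per-commune variance: V = s² + 2[ρ(1 − B) + (1 − ρ)/n] = s² + 2[0.25 × 0.60 + 0.75/10] = s² + 0.45.
- With s² = 0, the standard error is √(0.45/58) = 0.088. Noncentral t on 57 df gives power of 38.8% at 0.15 and 91.7% at 0.30, with a detectable effect of 0.251.
- With s² = 0.05 (assumed): 35.5%, 88.8% and 0.265, close to the stated 35%, 88% and 26%.
- With 10 versus 5 farmers and s² = 0: V = 0.30 + 0.75(1/10 + 1/5) = 0.525, giving 34.1%, 87.3% and 0.271.

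The test cannot tell a growth difference g_P − g_C from a programme effect of the same size. The power curve is therefore also the false-positive curve. With no true effect, 10 farmers per village and s² of 0 to 0.05:

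| Assumed shift (SD) | Rejection at nominal 5% |
|---|---|
| 0.05 | 8–9% |
| 0.10 | 19–20% |
| 0.15 | 36–39% |
| 0.20 | 56–61% |

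These shifts are assumptions that show sensitivity. They do not estimate what happened.

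**4. HGSF+ against regular feeding.** Two orders of events are possible.

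- *The design section is right and allocation had occurred before listing.* Nominators could have known which feeding arm they were in.
- *Appendix 1 is right and allocation uses baseline data.* Nominations preceded it, so knowledge of that allocation could not have shaped the lists for this contrast.

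The project-versus-control concern does not depend on which is right.

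**The case against.** A reader might infer that the nominated samples do differ by arm. The documents do not support that. One question, already hypothetical, is described for all villages. The caps of 10 and 5 apply to farmers to be interviewed, and lists could be longer, so the caps show what the survey team knew and not what chiefs or CGSs knew. The Discussion names only stakeholders at different levels, just after a sentence on regional and commune policy makers. This stands: the supportable word is may.

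A reader might also count the nominees' status as intended sellers as bias. It is not spurious in itself. Income earned by selling to the programme is caused by the programme, and under a true null that status alone creates no difference. It can change whose effect is measured. Only a difference in growth that would have occurred anyway biases the estimate.

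In the regular-feeding villages mayors mostly buy through traders, so a direct village purchase is less likely there. This weakens the mechanism in about half the project villages. It does not remove it, because CGS procurement is allowed.

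Finally, difference-in-difference handles fixed gaps, and an operations manual that is not shown may govern interview order. The first is partial mitigation, as step 2 shows. The second is possible, but the article describes the nomination procedure in some detail and mentions no safeguard.

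**Conclusion.** The concern holds as a risk of identification bias after allocation in the project-versus-control comparison of farm income. It rests on three things: reading the article's sequence (allocation, then listing) as the order of events, the absence of any described masking of nominators, and the CGSs' possible part in procurement or supplier identification. Its size cannot be estimated from the documents, and any figure in percentage points would be assumption alone. For HGSF+ against regular feeding it is conditional on the unresolved timing. The weakness is worth correcting while baseline work continues, but it is not evidence that the farm-income comparison is already invalid.

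**What to change.** 1. **Villages still to be listed.** Trial status says the baseline is incomplete. There, obtain nominations before the village's allocation is discussed, use interviewers not told the arm, and apply the cap afterwards. For villages already listed, record whether nominators knew the allocation.
2. **Supporting analysis.** Keep the nominated-farmer analysis. Pre-specify beside it a farm-income analysis in the randomly drawn households that report farm production at baseline. There are 25 − 10 = 15 per project village and 20 − 5 = 15 per control village, chosen by the same rule in every arm (58 × 15 = 870 on each side before the restriction). The household questionnaire already has a farm-income module, and the final analysis plan has yet to be approved.
3. **If nominated and random households are pooled** under a common baseline-surplus threshold, stratify or weight by nomination status. Otherwise the mix differs by arm (10 of 25 against 5 of 20). A threshold alone would not cure the problem, because nominees above it remain in the set.
4. **Reconcile** the design section with Appendix 1 on when, and from which data, HGSF+ was allocated.

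Cost: a change of interview order, some interviewer masking and added analysis text, with no extra households. The random-draw analysis will contain fewer surplus sellers, so it will be less precise and its effect diluted. The number of those households that farm is not given. It supports the nominated-farmer analysis and does not replace it.

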### Threats to validity

The main potential threats to the internal validity of the study, including contamination, spill-over effects and Hawthorne-like effects were examined for each of the outcome indicators of Section Programme theory of the intervention. From Table 4 it seems that most threats could be avoided by:

i. assigning treatments to communes rather than to villages within communes in order to avoid contamination effects;

ii. avoid informing teachers and households of the control villages that the programme will be implemented after two years in order to avoid expectancy effects;

iii. adopting strategies in conducting cognitive and achievement tests that prevent teachers and children from over-performing.

**Table 4 T4:** Threats to internal validity

**Indicator**	**Metric**	**Spill-over and contamination**	**Hawthorne and placebo effects**
Schooling	Enrolment, attendance, drop-out and completion	Children may attend school from neighbouring communities to have access to meals	Expectation of coming programme in control villages
Cognitive ability	Raven’s matrices or other test	Very unlikely	Teachers’ and children’s attempts to over-perform in both project and control villages
Attention	Digit span or other test	Very unlikely	Teachers’ and children’s attempts to over-perform in both project and control villages
Learning achievement	Scores on language and math tests	Very unlikely	Teachers’ and children’s attempts to over-perform in both project and control villages
Physical growth	Anthropometric measures of height and weight	Children from other villages may access school meals	Very unlikely
PAL	Parents perceptions	Very unlikely	Very unlikely
Diet diversity	Household consumption	Very unlikely	Very unlikely
Micronutrient intake	Iron status, anaemia	Children from other villages may access school meals	Very unlikely
Income	Farm profits	Unlikely, if food purchases are made in control villages	Very unlikely
Social accountability	Parental monitoring and motivation	None at household level, possible at local Government level	Possible

Given the panel structure of the data there is a potential risk of differential attrition. However, it is difficult to predict why households or farmers from the control groups should respond to the interviews in different ways. Refusal to take part in the interview by households not benefiting from the project seems to be the main threat. However, as shown in the table above, the project has limited impact on household expectations in both project and control groups and, therefore, should have limited impact on response rates.

One issue with impact on cognitive development is that the observed impact can be the result of:

•Increased attention in school resulting from the energy meal (short term effect)

•Increased overall cognitive abilities resulting from protracted school feeding, school attendance, play time, social interactions …and so on… (long term effect)

A recent systematic review of school feeding interventions [26] observed that most evaluations have not been able to distinguish the two effects. This could be achieved through careful design of the intervention as the one shown in Table 5. Half of the project children are not given the meal on the day of the test until after the test, while half of the control children are given the meal before the test. The differences across columns (a-c and b-d) should produce the long term effect, while the differences across rows (a-b and c-d) should produce the short term effect. This approach will possibly be tested as a case study in a sub-sample of schools.

**Table 5 T5:** Teasing out short-term and long-term impact on cognitive development

	**Meal**	**No meal**
Project	a	b
Control	c	d

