**Figure 4 F4:**
[figure not shown]
Programme theory of school feeding and smallholder agriculture.

**Table 1 T1:** Programme impact on smallholder farmers

** Effects**	**Impact on smallholder farmers**	** Spill-over effects**
Output effects	Increase in farm profits	Increase in consumer prices
Distributional effects	Increase in farm profits	Decrease in large farmers’ profits
Stabilisation effects	Risk reduction	none

The programme introduces additional demand on the market. In Mali, the school feeding programme purchases food for schools at the Commune level, which includes several villages. Most Communes have food markets. Mayors purchase from traders in the commune. Traders in turn purchase food from, among other sources, small-holder farmers. The effect of the food purchases is a shift of the demand curve for food (say rice) to the right (movement from D_0_ to D_1_), as illustrated in Figure 5.

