**Figure 7 F7:**
[figure not shown]
Potential impacts of HGSF with small and large supply elasticities.

The two supply curves in Figure 7 can be seen as short- and long-term supply curves or elastic and inelastic with respect to risk and market factors. In any case, they illustrate the differential impact of HGSF on prices and output.

•If farmers are not able to provide the additional food demanded by HGSF (small supply elasticity – curve S_s_), then most of the effect of HGSF goes into prices and little impact on output. From a welfare perspective, producer surplus increases (farmers win), while consumer surplus may decrease (consumers may lose).

•If farmers provide any additional food demanded by using current input more intensively and by quickly changing use of fixed inputs (large supply elasticity – curve S_l_), then HGSF would have a large impact on output and a negligible impact on prices. From a welfare perspective producer surplus increases (farmers win) and consumer surplus increases as well (consumers win). For the benefit of both producers and consumers, therefore, a high supply elasticity is needed.

In general, we should expect the supply elasticity to be between the two extremes depicted and, therefore, the programme to have an impact on both prices and output. The impact on prices depends on the level of spatial market integration. In principle, if markets are efficient, prices for the same food items should be the same everywhere after an adjustment for transport costs. However, the literature on market integration suggests that transfer costs may create a wedge between prices at different locations, which allow prices in the two locations to vary in an uncorrelated way within a band [11]. In other words, if transport costs for an isolated commune are very high, food prices may increase up to a point when trade between the two locations takes place and prices are equalised. There is, therefore, a real possibility that food prices increase at the commune level and that these price effects are transmitted to consumers.

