### Comparing school feeding to no-school feeding (multi-site cluster randomized trial)

In the multi-site cluster randomized trial the sites are blocks and clusters are randomly assigned to treatment and control within each site. In each commune (site), two schools (clusters) are selected and randomly assigned to the treatment and the control groups. This is equivalent to conducting a randomization of schools stratifying by commune.

There are a total of 58 communes selected for the intervention and two schools are chosen by local education authorities in each commune. In each school/village, 25 households will be interviewed. Only families with children in the age range from 5 to 15 will be selected, which implies that some 55 children in each community and a total of more than 6,500 children will take part to the interviews. The average number of children aged 5 to 15 in rural Mali was 2.58 in 2006 based on the data collected by the DHS. Care will also be taken to obtain a sizable sample of farmers and potential providers of staples for school feeding in each village.

We calculate power and minimum detectable effect size for the following outcomes:

•enrolment rates

•test scores

•farm income

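### Commune-level assignment protects only the HGSF+ v regular comparison; school feeding v control is randomised within communes, so its farm-income estimate is net of any commune-wide gain

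*Protocol article*

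**What the plan says.** **Safeguard.** Under Threats to validity, item (i) of the measures by which most threats could be avoided is "assigning treatments to communes rather than to villages within communes in order to avoid contamination effects".

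**Allocation.** Random assignment and manipulation of treatments describes a design that "compares outcomes of school feeding versus a control group at the school level", with two schools in two villages per commune. Its allocation sentence is loosely worded ("Each school was then randomly assigned either to the treatment or to the school feeding intervention"), but Appendix 1 is clear: "In each commune (site), two schools (clusters) are selected and randomly assigned to the treatment and the control groups". Only HGSF+ v regular feeding is randomised by commune. The reason given is that mayor-level training and monitoring act on the whole commune, "affecting outcomes in schools where the HGSF+ programme is not implemented". The section also mentions a procedure to prevent contamination between the two schools, without describing it.

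**Income mechanism.** The text under Figure 1 makes one mayor's office responsible for procurement for all relevant schools in the commune. Impact on food security and smallholder agriculture says that "the school feeding programme purchases food for schools at the Commune level, which includes several villages", that most communes have food markets, and that the traders' suppliers need not live in the project villages. It expects income to rise through prices and quantities, and sees "a real possibility that food prices increase at the commune level".

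**Spill-over rating.** For income, Table 4 reads "Unlikely, if food purchases are made in control villages".

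**Power.** Appendix 1 (Income) gives 35% power for a 15% increase, 88% for a 30% increase, and a detectable increase of 26% at 80% power. The Conclusions of Appendix 1 round this to 25%.

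**The concern.** Item (i) does not describe how feeding v control is assigned, and that is the contrast with the better power for farm income. A within-commune contrast removes whatever the two villages share. If mayors' purchases lift demand or prices across the commune, or if traders buy from control-village farmers, that part of the gain appears in both arms and drops out of the difference. All 58 communes contain a treated school, so no commune without school feeding remains to show it.

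The Table 4 cell appears to run the wrong way. Food bought in control villages is the condition under which control farmers receive programme income, so it makes spill-over more likely.

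At stake is what a small or null income result means. A reader who trusts item (i) and Table 4 would take it as the total impact of school feeding on small-holders.

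**Working it through.** **Step 1. Which comparison does item (i) fit?**

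| Comparison | Unit randomised | Do the arms share a commune? | Item (i) true? |
|---|---|---|---|
| HGSF+ v regular | commune, 29 v 29 | no | yes |
| Feeding v control | village school, 58 pairs | yes | no |

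**Step 2. Reproduce the stated power.** The inputs from Appendix 1 and Table 7 are n = 10 farmers per village, ICC ρ = 0.25, between-site share B = 0.40, J = 2 schools, K = 58 communes and α = 0.05 (taken as two-sided). The SD is about equal to the mean, so 30% is about 0.30 SD. For a multi-site cluster trial, with τ² the between-commune variance of the effect,

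Var = {τ² + 4[(1−B)ρ + (1−ρ)/n]/J}/K, tested on F(1, K−1).

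With τ² = 0: (1−B)ρ = 0.15, (1−ρ)/n = 0.075, and Var = (4 × 0.225/2)/58 = 0.45/58 = 0.00776.

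| Setting | Power at 15% | Power at 30% | Detectable at 80% |
|---|---|---|---|
| Stated | 35% | 88% | 26% |
| n = 10, τ² = 0 | 38.8% | 91.7% | 25.1% |
| n = 10, τ² = 0.05 | 35.5% | 88.8% | 26.5% |
| n = 6.67 (harmonic mean of 10 and 5), τ² = 0 | 34.1% | 87.3% | 27.1% |

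The printed inputs alone give slightly higher powers than stated. Either small change comes close, so the stated figures are plausible. The formula contains no term for a gain that reaches control farmers.

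**Step 3. Effect of a shared gain.** Let s be the fraction of the income gain that also reaches control-village farmers. This is an assumption: the protocol says that the supply and demand elasticities are not known. The contrast then recovers (1 − s) × the true gain. For a true gain of 30%:

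| s | Apparent gain | Power, τ² = 0.05 | Power, τ² = 0 | True gain needed to show 26% |
|---|---|---|---|---|
| 0 | 30% | 89% | 92% | 26% |
| 0.10 | 27% | 82% | 85% | 0.26/0.90 = 29% |
| 0.25 | 22.5% | 66% | 71% | 0.26/0.75 = 35% |
| 0.50 | 15% | 36% | 39% | 0.26/0.50 = 52% |
| 0.75 | 7.5% | 13% | 13% | 0.26/0.25 = 104% |

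At s = 0.50 no model is needed: the apparent gain is 15%, for which the protocol itself states 35% power. If control-village sales are displaced, s is negative and the contrast overstates the gain.

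**Step 4. What could a randomised spill-over check detect?** Control-village farmers number 29 × 5 = 145 in HGSF+ communes and 145 in regular communes. For a two-arm cluster comparison, Var = 4[ρ + (1−ρ)/n]/58. With n = 5 this is 4 × (0.25 + 0.15)/58 = 0.0276, SE = 0.166. At 80% power (F(1, 56), two-sided) the detectable difference is about 47%. The same formula with n = 10 gives 43%, against 40% stated for HGSF+ v regular. The check is therefore weak and can only support the interpretation.

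**The case against.** The list is introduced as ways in which threats could be avoided, not as a claim that they have been, and item (i) is correct for HGSF+ v regular. The within-commune design is an openly argued trade-off between power and contamination, and a procedure against contamination between paired schools exists. Its details may stand in the full protocol.

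The protocol also limits the channel. The Markets section expects price effects only at HGSF+ sites, at most three times a year, mainly at the foire, which serves a village or group of villages, so some pairs may use different markets. Demand shifts less if food is bought outside the commune. The main hypotheses place the income impact on a few farmers in intervention villages, and purchases directed to them remain in the contrast. Simulations, monthly prices and possible later matched controls are planned.

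Most of this stands, and it limits the size of the problem. It does not remove it. Trader purchases from other villages are not confined to HGSF+ sites. Nothing in the article says that the contamination procedure reaches traders or prices. The simulations do not correct the randomised estimate.

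A reader might go further and infer that the income estimate is biased towards zero by design, so that a real benefit would be reported as no effect. The documents do not support that: s is not given, displacement could reverse the direction, and a near-null estimate needs s close to 100%.

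**Conclusion.** The point holds in limited form. Item (i) is true of HGSF+ v regular and untrue of school feeding v control, and the income cell of Table 4 makes spill-over unlikely on a condition that would cause it. By the protocol's own theory, the feeding v control income contrast excludes any gain shared across the commune, and its stated power and detectable increase assume that there is none.

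The size cannot be computed from the documents. With an assumed s of 25% to 50%, a true 30% gain would appear as about 22% to 15%. Power would be about 66–71% at the first and 35–39% at the second, against 88% stated. The price part of s would matter mainly in the 29 HGSF+ communes.

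It may also be tempting to make HGSF+ v regular the main income contrast. The documents speak against this: Appendix 1 gives it 50% power at a 30% increase and a 40% detectable increase, and calls the sample clearly insufficient for that purpose. It also estimates only the increment between two feeding arms, not the total effect against no programme.

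**What to change.** 1. In Threats to validity, restrict item (i) to HGSF+ v regular feeding, and say that feeding v control is randomised within communes.
2. Correct the income cell of Table 4: spill-over is possible, and likely if food is bought from control-village farmers.
3. State that the feeding v control income estimate is net of commune-wide effects and is not total impact, so a null result does not rule out a commune-wide benefit. State that the income power figures assume no spill-over.
4. As a secondary analysis, compare control-village farmers in HGSF+ communes with those in regular communes (29 v 29), alongside the planned monthly foire prices. This is a randomised check on spill-over from HGSF+ relative to regular feeding, not on spill-over from school feeding itself.
5. Keep the existing main income contrast.

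All the data are already planned, so the work is wording and one analysis. The price is a more limited income conclusion and a check that, on the planned farmer numbers, would detect only a difference of about 47%.
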